## Study procedures

See above, section 7.1

## Withdrawal of individual subjects

Subjects can leave the study at any time for any reason if they wish to do so without any consequences. The investigator can decide to withdraw a subject from the study for urgent medical reasons. In case of grade III/IV clinically relevant toxicities, which can’t be managed by standard procedures and interfere with the neuropsychological tests at day 5 of the dexamethasone courses, the investigator will decide to postpone study medication. The subject can restart study medication in the following dexamethasone course.

### Specific criteria for withdrawal (if applicable)

## Replacement of individual subjects after withdrawal

Enrolled subjects are all subjects who signed the informed consent form.

Evaluable subjects: All subjects who received two courses of study treatment (one placebo and one trial medication) and two on-treatment efficacy evaluations. Analyses of efficacy will be performed on the dataset of all efficacy-evaluable subjects.

Subjects will be enrolled until a total of 50 evaluable subjects is reached.

Patients who aren’t able to get dexamethasone or who have to quit during a course will have

to start over with study medication at a new following course of dexamethasone.

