**Objective**:

- The primary aim of the study is to reduce dexamethasone induced cerebral side-effects on mood, behaviour, and cognition by adding physiological doses of cortisol to standard treatment
- The secondary aim of the study is to analyse the effect of the intervention on other side-effects of dexamethasone; a descriptive intra-patient comparison of blood pressure, insulin levels, visceral fat gain, lipid profile and glucose levels between intervention treatment and placebo.
- The third aim of the study is to determine the positive predictive value positive predictive value of the salivary very low dose dexamethasone suppression test with cortisol as a novel in vivo diagnostic test, on dexamethasone side-effects.

**Study design:** A prospective double blind placebo-controlled randomized cross-over design.

**Study population:** 50 patients, aged 3-16 years, treated according to medium risk ALL treatment schedule will be included after informed consent.

**Intervention**: During 2 identical periods of 5 days of dexamethasone treatment, in addition, patients will receive either a physiological dose of cortisol (intervention) or placebo.

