# *7.* METHODS

## 7.1 Study parameters/endpoints

**Intervention**: We will study 50 children in a cross-over design. During dexamethasone treatment, patients will receive either placebo or cortisol in a physiological dose of 10 mg/m2/day divided in 3 doses with a circadian rhythm. Cortisol is available and registered for pediatric use in several oral preparations. No side-effects are expected because it is used in physiological dosages and long term experience with this drug has been obtained in various other patient groups.

Primary **outcome parameter** is the parent-reported strength and difficulty questionnaire in Dutch (SDQ-Dut) 20 after 5 days of dexamethasone treatment with or without cortisol. In the general population mean SDQ score is 7,0 (1 SD= 6,0)20 . We expect the mean SDQ-Dut score of the children after 5 days of dexamethasone treatment to be around 15 in the control group. Our aim is to have a SDQ score in the treated group, which is 1 SD lower (6 points) compared to the controls. Secondary outcome parameters are mood and behaviour questionnaires and (neuro-) cognitive tests and metabolic parameters (see below).

*Fig 2. Schematic study design*

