## The end of treatment point is at the end of day 5 of the second dexamethasone study course after completion of the neuropsychological tests. There is no follow-up planned or required except for monitoring of serious adverse events.

## Sample size calculation

Power analysis was performed on the mean outcome parameter SDQ. The mean of the SDQ scale is expected to be 7,0 with a standard deviation of 6,0. In the placebo effect we expect a rise of 8 points and a correlation of 64% between measurement at start and finish of the medication period. This correlation will result in a larger power as we will perform an analysis with the second measurement as outcome and first measurement and intervention as predictors.

Iizuka et al found that children with ADHD, who have behavioural and concentration problems, have a mean SDQ score of 16, which is one standard deviation above the general population.57 After simulating five hundred datasets we found that 40 children is enough to have 80% chance of finding a significant relationship (alpha = 0.05) when the effect of the intervention is 6 points (1 SD) on the scale. Considering the probability of drop-out, a total of 50 patients will be included.

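### The protocol sets two incompatible recruitment targets: 50 children included with drop-out already allowed for, and 50 evaluable children with no cap on enrolment

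*Protocol*

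**What the plan says.** The Protocol's sample size calculation (section 9) reports from simulation that "40 children is enough to have 80% chance of finding a significant relationship (alpha = 0.05) when the effect of the intervention is 6 points", and continues: "Considering the probability of drop-out, a total of 50 patients will be included". The summary, under study population, gives the same total as an intake figure: "50 patients, aged 3-16 years, treated according to medium risk ALL treatment schedule will be included after informed consent". Section 7.1 says "We will study 50 children in a cross-over design", which does not specify whether the 50 are those who start or those who finish.

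The section on replacement of individual subjects after withdrawal (7.5 in the table of contents) uses 50 for something else. It defines evaluable subjects as "All subjects who received two courses of study treatment (one placebo and one trial medication) and two on-treatment efficacy evaluations", bases the efficacy analyses on them, and sets the rule: "Subjects will be enrolled until a total of 50 evaluable subjects is reached". It adds that a child who cannot receive dexamethasone, or who has to stop during a course, starts again with study medication at a later course. The preceding section on withdrawal likewise allows study medication to be postponed to a later course, and lets any child leave at any time.

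**The concern.** In the sample size calculation, 50 is the result of adding a drop-out allowance to 40. In the replacement section, 50 is what must remain after drop-out. The same number cannot be both unless nobody drops out, and the calculation expressly expects some loss. If the replacement rule governs, the allowance is in effect applied twice: once in going from 40 to 50, and again by recruiting until 50 completers exist.

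At stake is how many children with leukaemia take part. The summary's total is 50, while the replacement rule has no upper limit. Suppose 50 children have been included and 42 are evaluable. One part of the protocol then says that intake is complete, and another says that recruitment continues.

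**Working it through.** **Inputs stated in the Protocol.** From the sample size calculation: 40 children for 80% power, alpha 0.05, effect 6 points, SD 6, correlation 0.64 between the start and finish of a medication period, and 50 included. From the replacement section: 50 evaluable. **Not stated:** the drop-out rate, a maximum enrolment, and the sidedness of alpha (taken below as two-sided).

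**Step 1: the plan's step from 40 to 50.** Dividing by the retained fraction gives 40 / (1 − d) = 50, so d = 1 − 40/50 = 0.20. The step is sound arithmetic for 20% loss, but that rate is back-calculated. The text says only that 40 children are enough; that these 40 are children remaining after drop-out is an inference. It is the reading that explains the step to 50.

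**Step 2: the two rules over a range of loss.** If 50 are included, the number evaluable is 50 × (1 − d). If 50 must be evaluable, the number needed is 50 / (1 − d), rounded up.

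| Assumed loss d | Evaluable if 50 included | Children needed for 50 evaluable | Excess over 50 |
|---|---|---|---|
| 0% | 50 | 50 | 0 |
| 5% | 47.5 | 50/0.95 = 52.6, so 53 | 3 |
| 10% | 45.0 | 50/0.90 = 55.6, so 56 | 6 |
| 15% | 42.5 | 50/0.85 = 58.8, so 59 | 9 |
| 20% | 40.0 | 50/0.80 = 62.5, so 63 | 13 |
| 25% | 37.5 | 50/0.75 = 66.7, so 67 | 17 |

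The rules coincide only in the first row. Loss here means a child who never becomes evaluable. A child who interrupts a course and completes a later one is not lost, so the restart provision moves the trial up the table by an amount that the Protocol does not let us estimate.

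**Step 3: does power require 50 evaluable?** The least favourable simple model ignores both the pairing and the baseline and treats the children as two separate groups. The requirement per group is 2 × (1.96 + 0.84)² × 6²/6² = 15.7, so 16, or 32 in all. With 40 children (20 per group), the standardised difference is 6 / (6 × √(2/20)) = 3.16, and power is Φ(3.16 − 1.96) = 88.5%. Adjusting for the first measurement with correlation 0.64 gives a residual SD of 6 × √(1 − 0.64²) = 4.61. Power with 40 is then about 98%, by formula and by a 5,000-dataset simulation. A paired cross-over comparison gives over 99% with 40, even if the correlation between periods, which is not stated, is taken as 0. So 40 is sufficient and conservative for the stated 80%, and 50 evaluable is not needed to reach it.

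**The case against.** The strongest reply is that the Protocol does state when recruitment ends: at 50 evaluable children, with evaluable defined in the same section. That is correct. A reader might infer that no stopping rule exists, but the fault is a clash between this rule and the totals in the summary and the sample size calculation. Section 7.1 is compatible with either.

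It can also be said that the section is headed as a replacement section, so replacement may be intended, and that restarting at a later course may keep losses small. Both points have force. The first means that replacement should not be ruled out as a solution. The second means that 63 is an illustration at a back-calculated 20%, not a forecast. Neither reconciles the passages, because children may still withdraw outright and the calculation allows for it.

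Three further readings are tempting and unsupported:

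- **Burden statement.** A reader might think that it is contradicted too, but the burden and benefit-risk texts give no number of children.
- **Definition of enrolled.** The replacement section says "Enrolled subjects are all subjects who signed the informed consent form", and a reader might infer that screen failures shift the stopping point. They do not, because the rule counts evaluable children.
- **Power or bias.** A reader might suspect a loss of power or results-driven stopping. Power is adequate under either rule. No interim analysis is planned and blinding holds until the last patient's last visit, so the documents show no route to bias.

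**Conclusion.** The point holds as an internal contradiction in the sample size, wrong as written. At the 20% loss implied by 40/50, the two rules differ by 13 children (63 against 50, or 26%). Over an assumed 5 to 25% loss the difference runs from 3 to 17, and it is smaller to the extent that interrupted children become evaluable later. The size therefore rests on a drop-out rate that the Protocol does not give. The contradiction itself needs no assumption beyond at least one child being lost.

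The consequence is an undefined and uncapped number of children exposed beyond the stated 50. The analysis and its error rate are unaffected. It should be fixed, but it does not threaten the validity of the result.

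**What to change.** State one rule and use it in the summary, section 7.1, the replacement section and the sample size calculation. Either of two versions would do; the sponsor should choose.

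1. **Follow the sample size calculation.** Replace the enrolment sentence in the replacement section with: *50 children will be randomised, expected to give at least 40 evaluable.* The cost is one sentence and no extra children. The downside is that the evaluable number may fall below 50, which the calculation already allows for. The expectation of 40 holds for losses up to 20%.
2. **Keep 50 evaluable with replacement.** State the assumed drop-out rate and a maximum enrolment in the summary and the sample size calculation. The cost is a few sentences and an openly declared larger intake (56 at 10% loss or 63 at 20%, for example), which the power calculation does not require.

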## Follow-up of subjects withdrawn from treatment

Treated subjects are all subjects who received at least one dose of study treatment. Demographic and baseline characteristics and safety analyses will be performed on all treated subjects.

## Premature termination of the study

The Principal Investigators can decide to premature termination of the study on the following criteria:

- There is evidence of an unacceptable risk for trial subjects (i.e. safety issue)

- There is reason to conclude that it will not be possible to collect the data necessary to

reach the study objectives and it is therefore not ethical to continue enrolment of more

patients. The PI’s will notify the METC and the competent authority within 15 days, including the reasons for the premature termination.

# SAFETY REPORTING

## Section 10 WMO event

In accordance to section 10, subsection 1, of the WMO, the investigator will inform the subjects and the reviewing accredited METC if anything occurs, on the basis of which it appears that the disadvantages of participation may be significantly greater than was foreseen in the research proposal. The study will be suspended pending further review by the accredited METC, except insofar as suspension would jeopardise the subjects’ health. The investigator will take care that all subjects are kept informed.

## Adverse and serious adverse events

Adverse events are defined as any undesirable experience occurring to a subject during the study, whether or not considered related to [the investigational product / the experimental treatment]. All adverse events reported spontaneously by the subject or observed by the investiga­tor or his staff will be recorded.

A serious adverse event is any untoward medical occurrence or effect that at any dose:

- results in death;
- is life threatening (at the time of the event);
- requires hospitalisation or prolongation of existing inpatients’ hospitalisation;
- results in persistent or significant disability or incapacity;
- is a congenital anomaly or birth defect;
- is a new event of the trial likely to affect the safety of the subjects, such as an unexpected outcome of an adverse reaction, lack of efficacy of an IMP used for the treatment of a life threatening disease, major safety finding from a newly completed animal study, etc.

**NOTE** 1:

• Pregnancy: Incidence of pregnancy is not considered a SAE; pregnancy must, however, be reported immediately by E-mail to the principal investigators of this study;

• Overdose: All cases of overdose must be reported immediately by E-mail to the principal investigators of this study.

**NOTE 2**:

Criteria for hospitalizations not reported as SAEs include admissions for:

- Planned as per protocol medical/surgical procedure

- Routine health assessment requiring admission for baseline/trending of health status documentation

- Medical/surgical admission for purpose other than remedying ill health state (planned prior to entry into study trial; appropriate documentation required)

- Admission encountered for other life circumstance that carries no bearing on health status and requires no medical/surgical intervention (e.g. lack of housing, economic inadequacy, care-giver respite, family circumstances, administrative)

- Admissions for protocol-scheduled procedures or blood product transfusions will not be considered SAEs.

All SAEs occurring during the study or 16 days after the last administration of the trial medication, must be reported to the principal investigator within 24 hours of occurrence in order to comply with regulatory requirements. Adverse events classified as "serious" must be recorded on the SERIOUS AE (SAE) page of the CRF.

SAE reporting by TELEPHONE, FAX and E-MAIL:

DCOG –ECTC Safety Desk, [contact], [contact]

E-mail to: [[contact]](mailto:[contact]), [[contact]](mailto:[contact]), [[contact]](mailto:[contact]) and [[contact]](mailto:[contact])

Collection of complete information concerning SAEs is extremely important. If only limited information is initially available, follow-up reports are required. Thus, follow-up information which becomes available as the SAE evolves, as well as supporting documentation (e.g., hospital discharge summaries and autopsy reports), should be collected subsequently, if not available at the time of the initial report, and immediately sent using the same procedure as the initial SAE report. For ongoing SAEs a follow-up report should be sent at least once-monthly. The investigator is responsible for submitting these follow-up reports for all SAEs, until the SAE has resolved or until the patient’s condition stabilizes (in the case of persistent impairment), or the patient dies.

All SAEs will be reported through the web portal *ToetsingOnline* to the accredited METC that approved the protocol, within 15 days after the sponsor has first knowledge of the serious adverse reactions.

SAEs that result in death or are life threatening should be reported expedited. The expedited reporting will occur not later than 7 days after the responsible investigator has first knowledge of the adverse reaction. This is for a preliminary report with another 8 days for completion of the report.

### Suspected unexpected serious adverse reactions (SUSAR)

Adverse reactions are all untoward and unintended responses to an investigational product related to any dose administered.
Unexpected adverse reactions are adverse reactions, of which the nature, or severity, is not consistent with the applicable product information (e.g. Investigator’s Brochure for an unapproved IMP or Summary of Product Characteristics (SPC) for an authorised medicinal product).
The principal investigators are responsible for reporting SAEs/SUSARS to the IRB or other applicable regulatory authority.

In accordance with local regulations, the trial bureau will notify Investigators of all AEs that are serious, unexpected, and certainly, probably, or possibly related to the investigational product. This notification will be in the form of a SUSAR report.

Upon receiving such notices, the Investigator must review and retain the SUSAR reports with the Investigator Brochure. Where required by local regulations or when there is a central Institutional Review Board (IRB)/Independent Ethics Committee (IEC) for the study, the Sponsor will submit the SUSAR report to the appropriate IRB/IEC. The sponsor, together with the principal investigators, will determine if the informed consent requires revision.

The sponsor will report expedited the following SUSARs through the web portal *ToetsingOnline* to the METC:

- SUSARs that have arisen in the clinical trial that was assessed by the METC;

The remaining SUSARs are recorded in an overview list (line-listing) that will be submitted once every half year to the METC. This line-listing provides an overview of all SUSARs from the study medicine, accompanied by a brief report highlighting the main points of concern.

The expedited reporting of SUSARs through the web portal ToetsingOnline is sufficient as notification to the competent authority.

The sponsor will report expedited all SUSARs to the competent authorities in other Member States, according to the requirements of the Member States.

The expedited reporting will occur not later than 15 days after the sponsor has first knowledge of the adverse reactions. For fatal or life threatening cases the term will be maximal 7 days for a preliminary report with another 8 days for completion of the report.

### Annual safety report

In addition to the expedited reporting of SUSARs, the sponsor will submit, once a year throughout the clinical trial, a safety report to the accredited METC, competent authority, Medicine Evaluation Board and competent authorities of the concerned Member States.

This safety report consists of:

- a list of all suspected (unexpected or expected) serious adverse reactions, along with an aggregated summary table of all reported serious adverse reactions, ordered by organ system, per study;
- a report concerning the safety of the subjects, consisting of a complete safety analysis and an evaluation of the balance between the efficacy and the harmfulness of the medicine under investigation.

## Follow-up of adverse events

All adverse events will be followed until they have abated, or until a stable situation has been reached. Depending on the event, follow up may require additional tests or medical procedures as indicated, and/or referral to the general physician or a medical specialist.

## Data Safety Monitoring Board (DSMB)

A DSMB will not be installed in this study. The patients are treated for a short

time frame (5 days) and the drugs under investigation are well characterised and are given in a physiological dose, which is known for not harming patients. However, the data will be monitored as described in section 12 of this protocol.

# STATISTICAL ANALYSIS

The particular strength of this cross over design is that the interventions under investigation are evaluated within the same patients and so eliminates between-subject variability.

To prevent carry-over effect of treatments across study periods, a wash-out period is present and with the blinded randomisation the patient will start with either placebo or trial medication in a randomised fashion.

Given that the subjects act as their own controls, the analyses are based on paired data analysis.

Primary outcome parameter is the SDQ (continuous parameters). The effectiveness of treatments is assessed by comparing the effects of placebo and trial medication on SDQ by a two-way analysis of variance, with treatment order as a between-subjects factor and treatment type as a within-subject factor.

Secondary outcome parameters are mood and behaviour questionnaires, (neuro-) cognitive tests and metabolic parameters (all continuous parameters). The effectiveness of treatments is assessed by comparing the effects of placebo and trial medication on secondary outcome parameters by a two-way analysis of variance, with treatment order as a between-subjects factor and treatment type as a within-subject factor.

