For individual profiles of corticosteroid sensitivity the following data will be obtained: salivary diurnal cortisol rhythm (area under the curve), salivary very low dose (0,25 mg) dexamethasone suppression test27. This will be performed one week before start of the first study dexamethasone course and can be done at home. Salivary samples could be send to the endocrinology labarotory.

Table 2.: **Schedule Dexamethasone suppression test at home**

| **Time** | **Day 1** | **Day 2** |
| --- | --- | --- |
| awakening | Salivary sample (sober) | Salivary sample (sober) |
| 12am | Salivary sample |  |
| 4 pm | Salivary sample |  |
| 8 pm | Salivary sample |  |
| 8pm | 0.25mg dexa oral |  |

*Visits outpatient clinic*

Neuropsychological and metabolic outcome parameters will be obtained in both study courses at the first day and the fifth day of the dexamethasone course. At these days the patients will have to complete the questionnaires, fasting blood samples will be taken and neuropsychological test will be administered. Patients usually have a routine visit at the outpatient clinic the first day of each dexamethasone course. The fifth day study visit will be an extra visit for each patient.

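### The protocol states two different analyses of the primary SDQ endpoint, and its power argument belongs to only one of them

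*Protocol*

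**What the plan says.** The primary endpoint (section 7.1) is the parent-reported SDQ at the end of a five-day dexamethasone course. Neuropsychological outcomes, including the questionnaires, are "obtained in both study courses at the first day and the fifth day of the dexamethasone course", so each child has four SDQ scores: day 1 and day 5 of each course.

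The opening of the Statistical Analysis section assesses effectiveness by "comparing the effects of placebo and trial medication on SDQ by a two-way analysis of variance", with order as the factor between children and treatment as the factor within them. No day-1 score is named. The same section gives a general rule: "Given that the subjects act as their own controls, the analyses are based on paired data analysis".

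The Sample size calculation, in the same chapter, assumes an SD of 6.0, a rise of 8 points on placebo and a 64% correlation between the start and finish of a medication period. It says this correlation raises power because "we will perform an analysis with the second measurement as outcome and first measurement and intervention as predictors". That description names no child, period or order term. The univariate and multivariate headings that follow only refer back, and nothing ranks or reconciles the two descriptions.

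**The concern.** Both descriptions are written as the planned analysis of one endpoint, but they are different models. One leaves out the day-1 score and compares treatments within children. The other adjusts for the day-1 score and, as listed, contains no within-child structure. They can give different estimates, standard errors and p-values from the same data, and an analyst could defend either from the protocol after unblinding.

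The power argument is also tied to the second model only. The 64% correlation links day 1 and day 5 of the same course. The ANOVA depends on how strongly the two day-5 scores of one child are correlated across courses, and the protocol gives no value for that.

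**Working it through.** **Inputs from the protocol.** SD 6, effect 6 points, alpha 0.05 (taken as two-sided), within-course correlation r = 0.64, N = 40 (50 with drop-out).

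**Assumed.** Between-course correlation ρ, taken as equal for all pairs of scores from different courses unless stated. The protocol does not give it.

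**1. The plan's own figure (40 children for 80% power).** It is not reproduced under the stated inputs.
- Baseline-adjusted model read as two independent groups: residual SD = 6 × √(1 − 0.64²) = 4.61. This needs 10 per arm by normal approximation or 11 by t; 20 per arm gives 98% power.
- Cross-over ANOVA: SD of the within-child difference = 6 × √(2(1 − ρ)). This needs 18 children at ρ = 0, 11 at 0.5 and 9 at 0.64. With 40 children, power is at least 99%.

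The simulation settings behind the 40 are not given, so it may rest on unstated inputs. For the present point, what matters is that neither model leaves the trial short of power for 6 points.

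**2. Precision of the ANOVA and of the paired analysis with baseline (N = 40).**
- ANOVA: SE = 6 × √(2(1 − ρ)/40).
- Paired with baseline: the day-5 and day-1 within-child differences correlate at q = (0.64 − ρ)/(1 − ρ), so SE = ANOVA SE × √(1 − q²).

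| ρ | q | ANOVA SE | Paired + baseline SE |
|---|---|---|---|
| 0.3 | 0.34/0.70 = 0.486 | 1.12 | 0.98 |
| 0.5 | 0.14/0.50 = 0.28 | 0.95 | 0.91 |
| 0.64 | 0 | 0.80 | 0.80 |

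**3. The second model fitted literally, with 80 records treated as independent.**
- Reported SE = 4.61 × √(2/40) = 1.03, whatever ρ is.
- True variance of its estimate = 72 × (0.5904 − 0.1296ρ)/40, where 0.5904 = 1 − 0.64² and 0.1296 = (1 − 0.64)².
- ρ = 0.5: true SD = √(72 × 0.5256/40) = 0.97, so the reported SE is about 6% too wide.
- ρ = 0.6: true SD = √(72 × 0.5126/40) = 0.96, so it is about 7% too wide.

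The error is conservative. Simulated type I error was about 3–5% for ρ between 0.1 and 0.64. It fell to 0.3–2.4% in scenarios where the two day-1 scores were correlated at 0.64–0.8. The ANOVA held about 5% throughout.

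**4. How often the two stated models disagree.** This was simulated with 40 children, applying the ANOVA and the literal second model to the same data, over a range of assumed ρ.
- True effect 6 points: disagreement on significance in at most 0.4% of trials.
- 4 points (assumed): 0.4–12%.
- 2.5 points (assumed): roughly 17–27%.
- No effect: 5–6%.

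**The case against.** Four points can fairly be made for the plan.

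- **Pairing.** The sample-size sentence explains why a correlation helps power and is not a full model specification; the general rule on paired analysis may be meant to cover it. That is a reasonable reading. A reader might infer that the protocol plans to treat one child's two courses as independent, but the text does not establish this. What stands is that the listed predictors contain no pairing, so the sentence does not describe the ANOVA.
- **Validity of the ANOVA.** The two-way ANOVA is a proper paired cross-over analysis with correct type I error. Leaving out a baseline is a choice, not an error. This stands in full.
- **Size of the standard-error problem.** Dividing the unpaired SE of 1.03 by the SE of the better paired model might suggest standard errors 12–21% too wide at ρ of 0.5–0.6. That compares two different estimators. Against its own sampling error, the unpaired model is only about 6–7% too wide.
- **Power.** A reader might infer that the conflict leaves the trial too small. It does not: at the planned 6 points every reading gives at least 98% power with 40 children. The material disagreement arises only at smaller effects, which the protocol does not plan for.

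None of this reconciles the two descriptions. Nor is it detail left to a statistical analysis plan, since the protocol itself states both models.

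**Conclusion.** The point holds as a contradiction in stated text: one primary endpoint, two models, and a power rationale based on a correlation that does not enter the model named as the primary analysis. It should be fixed, but it does not threaten the trial's size or the validity of the ANOVA.

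The practical risk is a primary p-value that depends on which description is followed. It is negligible if the effect is near 6 points and real if the effect is much smaller. The 2.5-point effect and every between-course correlation used here are assumptions. The benefit of adding the baseline rests on that same unstated correlation: clear at 0.3, small at 0.5 and about nil near 0.64.

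**What to change.** State one primary analysis, in the same words, in the Statistical Analysis section and in the Sample size calculation. The suggested choice is the paired cross-over analysis of day-5 SDQ with treatment, period and order, adjusted for the day-1 SDQ of each course. With complete pairs, this is equivalent to analysing the within-child day-5 difference by order group with the day-1 difference as covariate. Delete the other description. Restate the power for the chosen model, giving an explicit assumed correlation between the two courses and a range around it.

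Keeping the ANOVA alone would also remove the contradiction, provided the 64% argument is dropped and the power is restated for it.

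The cost is protocol wording and a short power calculation. No new data are needed, because the SDQ is already completed "at the first day and the fifth day of the dexamethasone course" in both courses. The change should be made before unblinding.
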